## Abstract

**Background:**

Whilst there are comprehensive guidelines for the rehabilitation of people with severe impairments from stroke, there has been less attention on the health and rehabilitation needs of people with minor stroke. Our study will assess whether a new multi-component service pathway using an integrated model based around primary care will reduce unmet need following minor stroke compared with usual care 1 and 3 months post-hospital discharge.

**Methods:**

One hundred ten patients with minor stroke will be recruited within a parallel, randomised controlled trial design comparing a new service pathway and usual care.

The new service pathway will comprise a self-management kit, customised General Practitioner checklist, and a series of minor stroke educational topics. Participants will complete assessments pre-hospital discharge and 1 and 3 months later. The primary outcome measure will be the Survey of Unmet Needs and Service Usage. Secondary outcome measures will include assessments of ability, adjustment and participation; social group connectedness; return to work; health-related quality of life; and perceptions of the new service pathway (intervention group only). Mixed model repeated measures will be used to analyse within and between group differences at each time point. Return to work will be analysed using Chi square tests. Perceptions of the new service pathway will be analysed qualitatively.

**Dissemination of results:**

The project will produce an evidence-based, multicomponent service pathway for minor stroke patients, applicable to other health services nationally and internationally. Dissemination will include publications and presentations.

**Trial registration:**

Prospectively registered - Australian New Zealand Clinical Trials Registry (ACTRN12619000133134p) 30 January 2019.

## Background

Annually 15 million people worldwide experience a stroke [1]. Medical advances, such as stroke units and hyperacute treatments, have revolutionised acute stroke management. The lessening of stroke severity as a result of these advances has led to an increasing number of strokes classified as “minor”, and more individuals returning to community living post-stroke [2]. Minor stroke is now emerging as a significant health and social issue. Internationally, there are comprehensive guidelines for stroke rehabilitation; however, these guidelines focus on people with more significant impairments post-stroke, with minimal (if at any) information specific to minor stroke (e.g., [3–5]). This is compunded by contention in the literature about the definition of minor stroke [6], and frequent combining of minor stroke with transient ischaemic attack [7, 8].

Minor stroke (also mild stroke or non-disabling stroke) is a stroke where minimal motor deficits and/or no obvious sensory abnormalities are observed in hospital-based assessments [9]. These patients are typically discharged quickly from hospital. They are often left to seek help themselves and receive little ongoing rehabilitation support. Self-managing recovery in the community is challenging, as many patients are ill-equipped to locate services and supports [10] or uncertain about where to get appropriate advice [11]. This is concerning because unmet health, rehabilitation and/or social needs are associated with adverse health consequences, lower life satisfaction and poor psychological wellbeing [12–14]. A systematic review [15] demonstrated that people with minor stroke and their carers experience substantial challenges and disruptions adapting to life post-stroke. Additional research has found that only 69.9% of people with minor stroke return to work 3 months post-stroke [16]. Despite the high incidence of minor stroke in internationally and the personal and societal impact of ongoing limitations in functioning, there is no established pathway for minor stroke management beyond hospital discharge in many countries.

The SUN (Stroke Unmet Needs) study will respond to this problem. The overarching purpose is to compare the effect of a new multi-component service pathway (using an integrated model based on primary care following patients from hospital through to community) for minor stroke on unmet needs at 1- and 3-months post-discharge with patients receiving usual care. The SUN study builds on results of a needs analysis [17, 18] and aims to generate evidence-based recommendations by examining the extent to which the new pathway reduces unmet needs and improves Quality Of Life (QOL) compared to usual care.

### Primary aim

To determine whether a new multi-component service pathway for minor stroke reduces unmet need on the Survey of Unmet Needs (SUNSU) compared with usual care 1- and 3-months post-hospital discharge.

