### Hypothesis

The new pathway will reduce unmet needs at 1 and 3 months and improve functional outcomes, QOL, return to work and service access of minor stroke patients compared to usual care.

Note. Usual care (Control condition): This group will receive the usual care provided to minor stroke patients discharged from the recruiting hospital. This includes provision of an electronic discharge summary to the patient’s General Practitioner (GP) from the hospital treating team and a hospital outpatient follow-up appointment. Requirement for outpatient follow-up is determined at the time of discharge depending on the patient’s medical issues. Additionally, a My Stroke Journey booklet, discharge planning pack, counselling about stroke, medications and follow-up, are often available for patients, although this is not specific to minor stroke. Patients may be referred to private allied health providers or community services at the discretion of the treating team.

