### Sample size estimates

For a medium effect size (0.5) with 80% power for the 2 groups, 51 participants are required per group (calculated with G Power*2), increased to 55 to allow for dropout. Our previous project revealed that there were 2979 stroke admissions to the target hospital (Jan 2011-Jan 2017). Approximately 22% of stroke admissions met our inclusion criteria and were referred to our project, with 70% of eligible patients consenting to participate and being retained at follow-up.

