### Statistical analysis

Data entry and coding will be undertaken by the research assistant who conducts each assessment session. Missing data will not be entered. Quantitative data will initially be analysed using descriptive analysis (counts, means, standard deviations where appropriate). Mixed model repeated measures will be used to analyse within and between group differences at discharge, and 1 and 3 months on the SUNSU, MPAI, EXITS, SF-36, SSQOL, number of services used, and hospital readmissions. Analyses will occur blinded to group allocation. Subgroup analyses will occur if required. Return to work outcomes will be analysed using Chi square tests. Semi-structured interviews will be analysed using qualitative content analysis [30]. It is not anticipated that interim analyses will occur.

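### The primary SUNSU aim covers both 1 and 3 months, but no primary time point or single contrast is named and the sample size covers only one comparison

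*Protocol article*

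**What the plan says.** All of this comes from the protocol article.

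- **Primary aim:** the question is whether the pathway "reduces unmet need on the Survey of Unmet Needs (SUNSU) compared with usual care 1- and 3-months post-hospital discharge". Both visits carry equal weight.
- **Hypothesis:** "The new pathway will reduce unmet needs at 1 and 3 months". The statement is joint and directional.
- **Statistical analysis:** a mixed model for repeated measures will examine "within and between group differences at discharge, and 1 and 3 months" on the SUNSU and the other scales. The Abstract likewise plans group comparisons visit by visit. Neither place picks one visit or one overall group contrast as the primary test.
- **Sample size estimates:** "For a medium effect size (0.5) with 80% power for the 2 groups, 51 participants are required per group", then "increased to 55 to allow for dropout". Neither alpha nor sidedness is given, and nothing says which visit the calculation refers to.

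**The concern.** A trial with one primary scale and two post-discharge visits needs to say what counts as success: one named visit, both visits, either visit with alpha shared, or one contrast over both. The article fixes a two-visit aim and a one-comparison sample size, and these do not match. Each way of keeping two primary comparisons has a cost that the sample size does not cover. If either visit suffices at full alpha, the false-positive rate rises. If both are needed, power falls.

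The visits are not interchangeable. The education sessions are weekly (Intervention section), so only about four could take place by 1 month. A result at one visit and not the other is plausible, and the article as written cannot say whether such a trial succeeded.

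**Working it through.** **Inputs from the article:** standardised difference d = 0.5; power 80%; n = 51 evaluable per group; equal allocation; two post-discharge visits.

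**Assumptions (not in the article):** alpha 5%, tried one-sided and two-sided; correlation r between the 1- and 3-month test statistics of 0.5-0.7, with 0-0.9 as the wide range; the same effect of 0.5 at both visits; no baseline adjustment.

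**Step 1. Reproduce 51 per group.** With the exact t test, one-sided 5%, power is 79.9% at n = 50 and 80.6% at n = 51, so 51 is the smallest n that reaches 80%. Two-sided 5% needs 64 per group, and 51 gives 70.6%. At alpha 5%, the stated figure therefore reproduces only as a one-sided test of one comparison.

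The normal approximation used below has noncentrality δ = 0.5 × √(51/2) = 2.525. Single-test power is Φ(2.525 − 1.645) = 81.1% one-sided and Φ(2.525 − 1.960) = 71.4% two-sided.

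**Step 2. Either visit counts, each at 5%.** Two-sided false-positive rate = 1 − P(|Z1| < 1.96, |Z2| < 1.96). One-sided = 1 − P(Z1 < 1.645, Z2 < 1.645). Z1 and Z2 are standard bivariate normal with correlation r.

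**Step 3. Both visits must succeed.** Power = P(Z1 < δ − c, Z2 < δ − c) with the same correlation, where c = 1.645 or 1.960. The false-positive rate cannot exceed that of one test.

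| r | Either: false-positive, two-sided | Either: false-positive, one-sided | Both: power, one-sided | Both: power, two-sided |
|---|---|---|---|---|
| 0 | 9.75% | 9.75% | 65.7% | 51.0% |
| 0.5 | 9.1% | 8.8% | 70.2% | 57.4% |
| 0.7 | 8.3% | 8.0% | 72.7% | 60.7% |
| 0.9 | 7.0% | 6.8% | 76.2% | 65.3% |

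Starting from exact-t single-test power instead, the power figures at r = 0.5 and 0.7 are 69.5% and 72.0% one-sided, and 56.4% and 59.7% two-sided.

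**Step 4. Separate the two sources of loss.** At r = 0.5-0.7, requiring both visits on the one-sided basis takes power from 81.1% to 70.2-72.7%, a loss of about 8-11 points. Changing one test from one-sided to two-sided takes it from 81.1% to 71.4%, about 10 points, before the second visit is considered. The 57-61% figure contains both losses.

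**Step 5. Effect of baseline adjustment.** If the model uses the discharge score, and that score correlates b with each later visit, then δ becomes 2.525/√(1 − b²) and r becomes (r − b²)/(1 − b²). For r = 0.5-0.7, power to succeed at both visits is:

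- b = 0.3: 62-65% two-sided, 74-76% one-sided.
- b = 0.5: 71-74% two-sided, 82-84% one-sided.

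The article gives no value for b.

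**The case against.** The strongest reply is that this is a condensed article with an unseen analysis plan, and that a multiplicity rule is commonly left to such a plan. That is right as far as it goes, and the lack of a multiplicity rule is not by itself the point here. What stands is that the article itself fixes a two-visit aim and sizes one comparison. A later plan could reconcile them without more participants by choosing one visit or one overall contrast, but that would narrow the published aim.

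Two stronger readings are tempting, and the article supports neither.

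- A reader might infer that either visit can be called a success at full alpha, so that type I error is inflated. The article states no alpha and no such rule. The Primary aim and Hypothesis join the visits with *and*, which points to needing both, and then there is no inflation. The 8-9% is conditional.
- A reader might infer that the second visit alone pulls power from 80% to 57-61%. It does not: about 10 points of that gap come from two-sided testing.

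Two further objections have some force. The figures are unadjusted, while the planned mixed model includes the discharge assessment. With a baseline correlation of 0.5 and one-sided tests, power for both visits would be above 80%, so the shortfall is not certain under every set of assumptions. Also, the weekly-session argument concerns only one of three components, since the kit and checklist are handed over around discharge. It shows that the visits differ, not that 3 months must be primary.

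**Conclusion.** The point holds as a mismatch between a primary aim set at two visits and a sample size for one comparison, with no primary visit or contrast to join them.

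- **If both visits must succeed**, which fits the wording best, power is about 70-73% on the one-sided 5% basis that reproduces 51 per group, against the stated 80%. With two-sided 5% tests it is about 57-61%, where a single comparison has 71%. Type I error is not inflated.
- **If either visit counted at 5%**, the false-positive rate would be about 8-9%, or about 7-10% over correlations of 0-0.9.

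These are alternatives and cannot both apply. All of them rest on an assumed correlation (0.5-0.7 unless stated otherwise), and the power figures also on an unadjusted two-sample calculation with an effect of 0.5 at both visits. The structural point is certain from the text, while the figures are indicative. It should be corrected before the analysis.

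**What to change.** Name one between-group SUNSU contrast from the planned mixed model as the primary analysis. The 3-month contrast is one choice; a single overall contrast across both visits would also do. If one visit is chosen, make the other a secondary comparison tested only if the primary is significant. State alpha and sidedness beside the sample size, with the power that 51 per group then gives: about 71% at two-sided 5%, unadjusted, or about 81% at one-sided 5%. If baseline adjustment is relied on to raise this, state the assumed correlation.

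The text change is a few sentences and needs no extra participants. There are two costs. A positive result at the other visit alone could no longer be called a primary success, and the stated power may become less favourable.

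If the investigators want to keep both visits primary, the sample size has to follow (per group before dropout, unadjusted):

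- Both required, 80% joint power, r = 0.5-0.7: 65-62 one-sided, or 80-77 two-sided.
- Either sufficient, alpha halved to 2.5% per visit, 80% power at each: 64 one-sided, or 78 two-sided.

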### Secondary aims

To assess the effectiveness of the pathway on improving patients’ functional outcomes and QOL as measured by improved scores on the Mayo Portland Adaptability Inventory-4 (MPAI-4), Exeter Identity Transition Scales (EXITS), RAND 36-item Health Survey (SF-36), Stroke Specific Quality of Life Scale (SSQOL), and return to work 1- and 3-months post-hospital discharge compared to usual care.To explore patients’ perceptions of the new pathway.

### Hypothesis

The new pathway will reduce unmet needs at 1 and 3 months and improve functional outcomes, QOL, return to work and service access of minor stroke patients compared to usual care.

Note. Usual care (Control condition): This group will receive the usual care provided to minor stroke patients discharged from the recruiting hospital. This includes provision of an electronic discharge summary to the patient’s General Practitioner (GP) from the hospital treating team and a hospital outpatient follow-up appointment. Requirement for outpatient follow-up is determined at the time of discharge depending on the patient’s medical issues. Additionally, a My Stroke Journey booklet, discharge planning pack, counselling about stroke, medications and follow-up, are often available for patients, although this is not specific to minor stroke. Patients may be referred to private allied health providers or community services at the discretion of the treating team.

## Methods

### Design

In accordance with the Medical Research Council approach [19] for developing complex healthcare interventions, step 1 (needs analysis) [17, 18] has been completed. The current study represents the second step in developing a complex healthcare intervention (Phase II trial). The current project will use a parallel, cross-sectional from hospital to community, randomised controlled trial design (new service pathway compared to usual care) with follow up.

### Study setting

The study will span from a quaternary hospital through to primary care in the community in Queensland, Australia.

### Participants

One hundred ten participants diagnosed with minor stroke will be recruited while admitted as an inpatient following a minor stroke (See Fig. 1).

**Fig. 1 Fig1:**
[figure not shown]
CONSORT diagram of study procedure

### Inclusion and exclusion criteria

Admitted to the recruiting hospital with first ever stroke with minor deficits at the time of discharge (total length of stay in hospital < 2 weeks inclusive of all episodes of care) and having scores on the National Institute of Health Stroke Scale (NIHSS [20], score 0–5) consistent with minor or no obvious deficits. Aged > 18 years (no upper limit) and have no other neurological conditions as documented by the acute stroke team. Patients with a previous history of stroke will be excluded.

### Sample size estimates

For a medium effect size (0.5) with 80% power for the 2 groups, 51 participants are required per group (calculated with G Power*2), increased to 55 to allow for dropout. Our previous project revealed that there were 2979 stroke admissions to the target hospital (Jan 2011-Jan 2017). Approximately 22% of stroke admissions met our inclusion criteria and were referred to our project, with 70% of eligible patients consenting to participate and being retained at follow-up.

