### Screening and randomisation

In the 24 h prior to hospital discharge, patients will be screened for eligibility and recruited. The recruitment strategy will involve a two-stream approach over an approximately 6-month period. In the first stream, potential participants will be identified by the stroke team. The second stream will involve pre-screening for potential participants using PowerTrials. Following potential participant identification, a member of the stroke team or a research assistant will approach all eligible people with minor stroke admitted to the recruiting hospital, thus allowing a fair recruitment strategy. Participants will be randomly allocated to receive usual care or the new service pathway. Randomisation will occur using a computerised random number generator (by the primary researcher) with 50:50 assignment to the new pathway or usual care (*N* = 55 participants per group). Assignment will be concealed using opaque envelopes. The participants and their families and the research assistant conducting the assessment sessions will be blinded to the intervention assignment. No circumstances are foreseen which will necessitate unblinding; however, if unblinding is required, the unblinding process for an individual participant will be conducted by the primary researcher.

Participants will consent to participate in the project using a written Participant Information and Consent Form (PICF). PICFs will be provided to potential participants by a member of the stroke team or research assistant. Potential participants will be informed that participation in the trial is entirely voluntary and that they can opt out of the trial.

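### The 51 per group quoted for 80% power at an effect size of 0.5 matches an undeclared one-sided 5% t-test; under a two-sided 5% unadjusted comparison, 51 per group gives about 71% power

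*Protocol article*

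**What the plan says.** All references are to the protocol article.

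- **Sample size estimates** makes a definite claim: "For a medium effect size (0.5) with 80% power for the 2 groups, 51 participants are required per group". It attributes the figure to G*Power. The number is then "increased to 55 to allow for dropout".
- **Screening and randomisation** carries the 55 per group into the design, "with 50:50 assignment to the new pathway or usual care". The Abstract and the Participants section give the resulting total of 110.
- **Hypothesis** is directional: "The new pathway will reduce unmet needs at 1 and 3 months".
- **Statistical analysis** plans the analysis of the primary outcome, the SUNSU, as follows: "Mixed model repeated measures will be used to analyse within and between group differences at discharge, and 1 and 3 months".

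No section gives a significance level, says whether the tests are one- or two-sided, or states a correlation between repeated measurements. The effect size is given only in standardised form, without a SUNSU point difference or standard deviation. I read it as a standardised mean difference.

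**The concern.** An effect size of 0.5 with 80% power is a very familiar sample size input. With a two-sided 5% test it gives 64 per group, not 51. A reader who applies the usual convention finds the stated requirement 13 per group too low, which is 20% of 64 (13/64).

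This figure fixes the trial's total. If the primary comparison is tested two-sided at 5% without adjustment, the chance of missing a true effect of 0.5 is about 29% rather than the advertised 20%, and a null result would be read with more confidence than it deserves. If a one-sided 5% test was meant, the stated power is right. In that case, however, the chance of a false positive in favour of the pathway is 5%, twice the 2.5% of a two-sided 5% test, and that choice has to be visible before the data are seen.

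**Working it through.** **Inputs.** From the article: d = 0.5, power 80%, 1:1 allocation, 51 evaluable per group, 55 randomised per group. Assumed, because not stated: alpha = 5%, and a comparison of two means at one time point.

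**Step 1: reproduce the stated 51.** The normal approximation is n per group = 2(z_alpha + z_power)²/d².

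- One-sided 5%: 2 × (1.645 + 0.842)²/0.25 = 49.5, so 50. The exact noncentral t solution is 50.15, so **51**, with 80.6% power. This is the article's figure.
- Two-sided 10% gives the same result (50.15, so 51).

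**Step 2: the same calculation, two-sided 5%.**

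- Normal approximation: 2 × (1.960 + 0.842)²/0.25 = 62.8, so 63.
- Exact noncentral t: 63.77, so **64** per group.

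**Step 3: power of the planned numbers, two-sided 5%.** The noncentrality is d × √(n/2).

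| Evaluable per group | Noncentrality | Power, normal | Power, exact t |
|---|---|---|---|
| 51 | 0.5 × √25.5 = 2.525 | 71.4% | **70.6%** |
| 55 (no loss) | 0.5 × √27.5 = 2.622 | 74.6% | **73.8%** |
| 64 | 0.5 × √32 = 2.828 | – | 80.1% |

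**Step 4: detectable effect.** With 51 per group, two-sided 5% and 80% power, the normal approximation gives d = 2.802 × √(2/51) = 0.555. The exact t solution is **0.56**.

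**Step 5: could the planned model rescue the figure with a two-sided 5% test?** Each route needs a correlation that the article does not give.

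- *Adjustment for baseline SUNSU.* The variance is multiplied by (1 − r²). Setting 63.77 × (1 − r²) ≤ 51 gives r² ≥ 0.200, so r ≥ 0.447, or about 0.45. Exact t power at 51 per group:

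| r | Power |
|---|---|
| 0.30 | 74.6% |
| 0.40 | 77.9% |
| 0.45 | 80.0% |
| 0.50 | 82.3% |
| 0.60 | 87.8% |

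- *Group effect averaged over repeated measurements* (f = 0.25, noncentrality N f² m/(1 + (m − 1)ρ), where N is the total sample and m the number of measurements). With two measurements, 49 per group are needed at ρ = 0.5, 52 at ρ = 0.6 and 55 at ρ = 0.7. With three, 48 at ρ = 0.6 and 52 at ρ = 0.7.

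**Step 6: the allowance for loss.** Going from 51 to 55 allows for 4/55 = 7.3% loss.

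**The case against.** The strongest reply is that the article never says the test is two-sided or that alpha is 5%. Its aim and hypothesis are directional, and a one-sided 5% test with 51 per group delivers 80.6%. Alpha and sidedness may also sit in a full protocol or analysis plan that is not shown. Further, 70.6% is the power of an unadjusted two-sample test at one time point, whereas the planned analysis is a mixed model over three time points, which can be more efficient.

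Much of this stands. A reader might infer that the trial is simply underpowered and that the calculation was run with a one-tailed setting that conflicts with the analysis. The documents do not support that. The analysis section is silent on sidedness, so there is no stated conflict. The one-tailed setting is inferred from the match in Step 1. Step 5 shows that a baseline-adjusted two-sided analysis could reach 80% with a moderate correlation.

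The reply does not remove the point, for three reasons. A directional hypothesis does not declare a one-sided test; many superiority trials state a direction and test two-sided. The rescue by repeated measurements depends on correlations stated nowhere, and averaging over follow-ups does not apply if the groups are compared at each time point, as the Abstract says. And the point is not merely that alpha is omitted: the article prints a definite requirement that holds only under settings it does not disclose.

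A reader might also take the 70% figure in the same section as expected retention and conclude that power is far lower still. That is not supported. The 70% describes eligible patients who consented and were retained, taken together, so retention among randomised participants cannot be separated from it and may be well above 70%.

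**Conclusion.** The point holds in conditional form. The stated 51 per group is reproduced exactly, for a simple two-group comparison, by a one-sided 5% (or two-sided 10%) t-test that neither the sample size section nor the analysis section declares. If the primary test is a two-sided 5% unadjusted comparison, the statement is wrong as written: 64 evaluable per group are needed, power at 51 is about 71%, which is roughly 9 points short, and 80% power is reached only for an effect of 0.56.

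This rests on reading 0.5 as a standardised mean difference and on the 5% level, which is assumed. It does not establish that the trial as finally analysed will have less than 80% power.

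**What to change.** Keep the total at 110. State alpha and sidedness in both Sample size estimates and Statistical analysis, and base the sample size statement on the same test as the primary analysis. Then take whichever applies:

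- **Two-sided 5%, unadjusted:** restate the power as about 71% for an effect of 0.5 with 51 evaluable per group, or equivalently 80% for an effect of 0.56.
- **Two-sided 5%, adjusted for baseline SUNSU:** specify the adjustment and state the assumed correlation between baseline and follow-up. About 0.45 or more is needed for 80% power at 51 per group.
- **One-sided 5%:** declare it in both sections. The figure of 51 then stands.

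The cost is a sentence or two in each section and no added participants. Under the first option the printed power becomes less favourable. Under the third the more lenient error rate becomes visible.
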